**Figure 1 fig1:**
[figure not shown]
The flowchart of the trial.

#### Ethics and registration

The study protocol was approved by the Medical Ethics Committee of Shuguang Hospital, Shanghai University of Traditional Chinese Medicine (approval number: 2025–1739–079-02) and registered with the International Traditional Medicine Clinical Trial Registry (ITMCTR2025002306) on April 12, 2025.

### Objectives

This study aims, through a randomized, double-blind, placebo-controlled trial, to evaluate the efficacy and safety of YFXJD combined with standard EGFR-TKIs therapy in NSCLC patients, explore its role in alleviating symptoms of TCM Qi-Yin deficiency, systematically assess the incidence and characteristics of treatment-related adverse events, and investigate its potential modulatory effects on serum inflammatory cytokines, peripheral blood lymphocyte subsets, and tumor markers.

### Participants

Participants will be recruited from patients with NSCLC who visited the outpatient clinic and inpatient ward of the Department of Oncology at Shanghai University of Traditional Chinese Medicine’s Shuguang Hospital. Diagnosis of NSCLC was confirmed through sputum and pleural effusion cytology examinations, bronchoscopy, lung biopsy, or histological examination of surgically resected tissue, in accordance with the 2022 edition of the “Guidelines for the Diagnosis and Treatment of Primary Lung Cancer” (10) issued by the National Health Commission. Clinical staging followed the 9th edition of the TNM classification system for lung cancer jointly published by the Union for International Cancer Control (UICC) and the American Joint Committee on Cancer (AJCC) in 2024 (11). Patients with clinical stage IV disease were selected. TCM diagnosis followed the criteria for Bronchopulmonary Carcinoma with Qi and Yin Deficiency Syndrome outlined in the 2016 “TCM Diagnosis and Treatment Guidelines for Malignant Tumors” (12) issued by the Tumor Professional Committee of the Chinese Association of Integrative Medicine: Primary Symptoms: Cough with little or no sputum, or scant frothy mucus; sputum may contain streaks of blood; five-heart heat (palms, soles, and chest); spontaneous sweating; fatigue. Secondary symptoms: Hoarseness, dry mouth and throat, insomnia; Tongue and pulse characteristics: Dry, cracked tongue with teeth marks, thin white or peeled coating, floating and rapid or deep, taut and fine pulse. A diagnosis is confirmed when two or more primary and secondary symptoms are present concurrently, combined with corresponding tongue and pulse findings.

### Inclusion criteria

Participants will be eligible if they meet all of the following criteria:Histologically or cytologically confirmed diagnosis of NSCLC.Radiologically confirmed stage IIIB, IIIC, or IV disease (according to the 9th edition of the AJCC Cancer Staging Manual) (11).Presence of a sensitizing EGFR mutation confirmed by a validated molecular testing method (e.g., ARMS-PCR or NGS) from tumor tissue or plasma ctDNA (Primary EGFR-TKIs resistance mutations such as KRAS mutations and PTEN deletion are not included).Planned to initiate first-line systemic therapy with osimertinib (80 mg orally once daily), without prior chemotherapy, immunotherapy, or definitive local therapy (including chemoradiotherapy) for the current disease.Diagnosed with Qi-Yin Deficiency Syndrome according to TCM principles, as assessed by a certified TCM physician.At least one measurable solid tumor per RECIST 1.1.Aged 18 to 80 years (inclusive).Karnofsky Performance Status (KPS) score ≥ 60.Estimated life expectancy of at least 6 months.Absolute neutrophil count (ANC) ≥ 1.5 × 10^9^/L; Platelet count ≥ 75 × 10^9^/L; Hemoglobin ≥ 90 g/L.Total bilirubin ≤ 1.5 times the upper limit of normal (ULN); Alanine aminotransferase (ALT) and aspartate aminotransferase (AST) ≤ 2.5 x ULN (or ≤ 5 x ULN if liver metastases are present).Serum creatinine ≤ 1.5 x ULN, or calculated creatinine clearance (CrCl) ≥ 50 mL/min (using the Cockcroft-Gault formula).Willing and able to provide written, signed informed consent to participate in the study, and to comply with all study procedures and visit schedules.

### Exclusion criteria

Participants will be excluded if they meet any of the following criteria:Known history of serious mental illness or cognitive impairment that, in the investigator‘s judgment, precludes the ability to provide informed consent or comply with the study procedures.History of active alcohol or drug abuse within the past year.Women who are pregnant, breastfeeding, or of childbearing potential who are unwilling to use a highly effective method of contraception during the study treatment period and for at least 3 months (or per specific EGFR-TKIs label requirement) there after.Uncontrolled or clinically significant cardiovascular disease, including but not limited to: symptomatic congestive heart failure (NYHA Class ≥II), unstable angina, myocardial infarction within the past 6 months, or uncontrolled arrhythmias.Poorly controlled hypertension (e.g., systolic blood pressure >150 mmHg or diastolic blood pressure >100 mmHg despite optimal medical management).Active, uncontrolled systemic infection requiring intravenous therapy.Any other severe, uncontrolled concomitant medical condition that, in the opinion of the investigator, would compromise the participant’s safety or interfere with the study evaluations.Receipt of any systemic anti-cancer therapy (including chemotherapy, immunotherapy, other targeted therapy, or investigational agents) within 4 weeks prior to the first dose of study treatment.Palliative radiotherapy to non-target lesions is permitted if completed >2 weeks prior to enrollment. Radiotherapy to target lesions or whole brain radiotherapy within 4 weeks prior to enrollment is excluded.Prior definitive chemoradiotherapy for stage III disease.Symptomatic, untreated, or unstable brain metastases or leptomeningeal disease requiring immediate local therapy (e.g., steroids, surgery, radiation). Participants with a history of treated brain metastases are eligible if they are radiologically stable (confirmed by MRI at least 4 weeks apart), asymptomatic, and do not require corticosteroid treatment for at least 2 weeks prior to the first dose.History of another primary malignancy.History of clinically significant interstitial lung disease (ILD), drug-induced ILD, or any evidence of active ILD on baseline imaging.Known severe hypersensitivity to any component of YFXJD or to osimertinib.Any condition that impairs oral drug absorption (e.g., inability to swallow, major gastrointestinal resection, active inflammatory bowel disease).

### Withdrawal/termination criteria

Participants will be withdrawn or terminated from the trial if any of the following conditions are met:Failure to adhere to the key procedures outlined in the study protocol, which may compromise the validity of the data obtained from that participant.The use of concomitant therapies that are prohibited by the protocol for the management of NSCLC or its symptoms.Discontinuation of osimertinib due to toxicity: Occurrence of severe adverse reactions attributable to osimertinib therapy that necessitate the permanent discontinuation of the targeted agent, as determined by the treating physician. This criterion focuses on adverse events (e.g., severe interstitial lung disease, hepatotoxicity, or intolerable grade 3/4 rash or diarrhea) that make continued osimertinib treatment unsafe.Withdrawal of consent: The participant voluntarily decides to withdraw from the study at any time for any reason.Loss to follow-up: The participant becomes unreachable or fails to attend scheduled study visits without providing reason, despite repeated attempts at contact by the research team.The principal investigator determines that continued participation is not in the best interest of the participant’s health and safety.

Participants who are discontinued from the study intervention will be encouraged to continue in the follow-up phase for the collection of survival and safety data, where feasible and with their consent. All reasons for withdrawal or discontinuation will be documented in the case report form.

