#### Follow-up and assessments

Follow-up visits will occur every 3 months, as outlined in Table 2, and will include clinical evaluation, imaging studies, laboratory testing, and assessment of adverse events. Imaging for tumor response assessment will be performed every 8 weeks from randomization until disease progression. The efficacy of YFXJD will be evaluated through progression-free survival, TCM symptom scores, activity levels, biochemical parameters, and exploratory biological indicators. Safety will be assessed according to protocol-defined criteria. The trial flowchart is presented in Figure 1.

**Table 2 tab2:** Schedule of trial.

Assessment/Time point	Screening	Baseline/Initiation	Treatment period	Treatment period	Long-term follow-up	End-of-treatment visit	Survival follow-up
	D -7	D0	D90 ± 7	D180 ± 7	D365 ± 7	Upon PD/Discontinuation	
Procedures							
Informed consent	✓						
Eligibility review	✓						
Data collection							
Demographic information	✓						
History of NSCLC & treatment	✓						
History of other diseases	✓						
Randomization & drug dispensing		✓	✓ (Re-supply)	✓ (Re-supply)			
Primary endpoints							
1. PFS (RECIST 1.1)			Imaging per protocol	Imaging per protocol	Imaging per protocol	✓ (Confirm PD)	Record death
2. TCM Syndrome Score	✓ (Baseline)		✓ (Interim)	✓ (Primary Time Point)			
Secondary endpoints (Efficacy)							
Tumor response (ORR/DCR)			✓	✓	✓	✓ (Final)	
Quality of life (EORTC QLQ)	✓ (Baseline)		✓	✓	✓		
Performance status (KPS)	✓ (Baseline)		✓	✓	✓		
Biomarkers							
Lymphocyte subsets	✓ (Baseline)		✓	✓	✓		
Inflammatory cytokines	✓ (Baseline)		✓	✓	✓		
Tumor markers	✓ (Baseline)		✓	✓	✓		
Safety assessments							
Clinical laboratory tests							
CBC, hepatic & renal function	✓	✓	✓	✓	✓	✓	
Urinalysis & stool routine	✓	✓	✓	✓	✓	✓	
AE/SAE collection	✓	✓	✓	✓	✓	✓	
EGFR-TKIs specific AE recording		✓	✓	✓	✓	✓	
Concomitant medication record		✓	✓	✓	✓		
Proportion with dose Mod./Disc.			Recorded	Recorded	Recorded	✓ (Final)	
Study administration							
Protocol deviation record		✓	✓	✓	✓		
CRF completion		✓	✓	✓	✓	✓	

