### Outcomes

#### Primary outcomes

Progression-Free Survival (PFS): Defined as the time from randomization to the first occurrence of radiographic disease progression according to RECIST 1.1 (15) criteria or death from any cause, whichever occurs first. Imaging will be performed every 8 weeks from randomization until disease progression, with blinded independent central review.

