### Sample size

The sample size for this study was calculated based on the primary outcome of progression-free survival (PFS). Based on the FLAURA trial, the median PFS for osimertinib monotherapy is approximately 18.9 months. To achieve 80% power at a two-sided significance level of α = 0.05 for detecting a clinically meaningful difference, a target hazard ratio (HR) of 0.66 was assumed, corresponding to a median PFS of approximately 28.6 months in the experimental group (an absolute extension of 9.7 months). This effect size is consistent with the HR observed in the CATLA trial (HR 0.68).

Using the Schoenfeld formula for the log-rank test, the required number of PFS events (d) is calculated as:
$$d=4\times {\left(Z\_(1-\alpha /2)+Z\_(1-\beta )\right)}^{2}/{\left(\ln\;\mathrm{HR}\right)}^{2}$$

With α = 0.05 (two-sided), β = 0.20 (power = 0.80), Z_(1-α/2) = 1.96, Z_(1-β) = 0.84, and HR = 0.66:
$$d=4\times {\left(1.96+0.84\right)}^{2}/{\left(\ln\;0.66\right)}^{2}\approx 176\;\text{events}$$

Under a 1:1 randomization ratio with an accrual period of 12 months, a minimum follow-up of 12 months, and an expected event rate of approximately 65% at the end of follow-up, the required total sample size is approximately 270 patients (135 per group). Accounting for an estimated dropout rate of approximately 20%, we plan to enroll 200 patients (100 per group) to ensure that sufficient patients complete the primary endpoint assessment. The planned enrollment of 200 patients is expected to yield approximately 130 PFS events, providing approximately 75% power at the planned analysis. An interim analysis for futility is planned after 50% of the expected PFS events have been observed, with the option to increase sample size if warranted by conditional power calculations.

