#### Handling of missing data

For the primary endpoint (PFS), censoring will be applied at the last known follow-up date for patients without a progression event. For other continuous variables with missing values, multiple imputation will be used for primary analyses, with sensitivity analyses using Last Observation Carried Forward (LOCF).

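### The withdrawal rule can end tumor imaging before progression, against the imaging rule for the primary endpoint, so some PFS data may be lost without need

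*Protocol article*

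**What the plan says.** **Withdrawal.** Under Withdrawal/termination criteria the protocol article states: "Participants will be withdrawn or terminated from the trial if any of the following conditions are met". One condition is "The use of concomitant therapies that are prohibited by the protocol for the management of NSCLC or its symptoms". Others that leave the patient reachable are failure to adhere to key procedures, permanent discontinuation of osimertinib for toxicity, and the principal investigator's judgment. The paragraph after the list says of patients who come off treatment that they "will be encouraged to continue in the follow-up phase for the collection of survival and safety data, where feasible and with their consent". Tumor imaging is not named.

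**Imaging.** Follow-up and assessments says: "Imaging for tumor response assessment will be performed every 8 weeks from randomization until disease progression". The PFS definition under Primary outcomes repeats this: "Imaging will be performed every 8 weeks from randomization until disease progression, with blinded independent central review". Neither sentence ties imaging to being on treatment.

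**Table 2.** The end-of-treatment visit is timed "Upon PD/Discontinuation". In the PFS row, the survival follow-up cell asks only for death to be recorded, while the long-term follow-up (D365) cell calls for imaging.

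**Censoring.** Under Handling of missing data, "censoring will be applied at the last known follow-up date for patients without a progression event". No separate rule is given for withdrawal or for prohibited therapy.

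**The concern.** Take a patient who starts a prohibited treatment while still progression-free. Staff who follow the withdrawal section may take the patient off the trial and collect only vital status and adverse events. Staff who follow the PFS definition would go on scanning every 8 weeks. Both rules are stated, and they lead to different primary-endpoint data for the same patient.

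If scans stop, the progression date is not observed and the patient is censored. Starting another treatment for the cancer or its symptoms may be a sign that progression is near, in which case the censoring is informative. A statistical analysis plan can say how to censor, but it cannot recover scans that were never taken. Many of these patients could still be scanned, so the loss is avoidable, unlike loss through withdrawn consent or lost contact.

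**Working it through.** **Reading the rules together, for a patient who starts prohibited therapy before progression**

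| Place in the article | What it implies for scans |
|---|---|
| Withdrawal/termination criteria | Leaves the trial; optional follow-up for survival and safety; scans not named |
| Follow-up and assessments; Primary outcomes | Every 8 weeks until progression, no exception |
| Table 2, PFS row, survival follow-up | Death only |
| Table 2, PFS row, long-term follow-up | Imaging continues |

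The survival follow-up column has no adverse-event or laboratory checks, whereas the long-term column has both. So the survival column alone cannot be the phase that collects safety data, and the table is ambiguous.

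**Inputs from Sample size:** median PFS 18.9 and 28.6 months, HR 0.66, 100 patients per arm, 12 months' accrual, 12 months' minimum follow-up, two-sided α 0.05. **Assumptions:** exponential PFS, uniform accrual, and 5, 10 or 20 of 200 patients withdrawn before progression at a common constant rate w, with imaging stopping then. The only loss figure in the document is about 20% dropout (40 of 200), not split by cause.

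**Step 1. The plan's event count.** The article states: "The planned enrollment of 200 patients is expected to yield approximately 130 PFS events". That is 200 × 65% = 130. Projecting from its own medians instead, with λ = ln 2 / median:

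P(event) = 1 − [exp(−12λ) − exp(−24λ)] / (12λ)

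- Placebo: 1 − (0.6440 − 0.4147)/0.4401 = 0.479, or 47.9 events.
- YFXJD: 1 − (0.7476 − 0.5590)/0.2908 = 0.351, or 35.1 events.
- Total: 83.0.

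The gap between 83 and 130 is a separate matter. Both are used below.

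**Step 2. Events lost if withdrawal is unrelated to risk.** For observation time t, averaged over 12 to 24 months:

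- withdrawn before progression = w/(λ+w) × [1 − exp(−(λ+w)t)]
- events still observed = λ/(λ+w) × [1 − exp(−(λ+w)t)]

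Power = Φ(√d/2 × |ln 0.66| − 1.96), which is 47.3% at d = 83.0.

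| Withdrawn | w per month | Events lost (placebo + YFXJD) | Left | Share | Power | Same share of 130 |
|---|---|---|---|---|---|---|
| 5 | 0.00184 | 0.71 + 0.55 = 1.26 | 81.8 | 1.5% | 46.8% | 1.97 |
| 10 | 0.00374 | 1.43 + 1.10 = 2.53 | 80.5 | 3.1% | 46.2% | 3.97 |
| 20 | 0.00774 | 2.89 + 2.22 = 5.11 | 77.9 | 6.2% | 45.0% | 8.00 |

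On the stated 130 events the same formula gives 65.9% power, falling to 65.2% (5 withdrawn) or 63.1% (20 withdrawn).

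**Step 3. Events lost if withdrawal is related to risk.**

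- Progression hazard tripled after withdrawal: 2.70 of 84.5 events (3.2%) for 5 patients, 10.93 of 88.9 (12.3%) for 20.
- Extreme case, every withdrawn patient progresses before the cut: 5/(81.8 + 5) = 5.8%, 20/(77.9 + 20) = 20.4%.

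**Step 4. Effect on the treatment estimate.** In a simulation of 2,000,000 patients per arm with a tripled hazard after withdrawal and w = 0.008 per month in both arms, the rate ratio is 0.669 with full follow-up and 0.662 with censoring. Equal withdrawal hardly moves it.

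All loss figures are ceilings for their scenario. They count every PFS event after withdrawal as lost, whereas a death recorded in survival follow-up still counts as a PFS event.

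**The case against.** The strongest reply is that the imaging rule is stated twice, once inside the primary-endpoint definition, and that only progression ends it. No sentence says that scans stop at withdrawal. The closing paragraph of the withdrawal section speaks of stopping the study intervention, so the list might be read as treatment discontinuation. The long-term follow-up column of Table 2 includes imaging. The article also condenses a fuller protocol, which may hold the off-treatment procedures.

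Much of this stands. The scans are already planned, and Table 2 cannot be cited as support for stopping them. It does not remove the conflict. The opening sentence refers to leaving the trial, the later follow-up is voluntary, and the data it names leave out imaging. This is a matter of what the article states, not of detail left to another document.

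A reader might infer three stronger things, none of which the document supports:

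- **The intention-to-treat analysis is contradicted.** It is not. These patients stay in the analysis set and are censored.
- **The hazard ratio is biased.** That would need unequal loss between arms. As a rough illustration, losing 5% of events on placebo and 15% on YFXJD gives 0.66 × 0.85/0.95 = 0.59, and the reverse gives 0.66 × 0.95/0.85 = 0.74. Nothing in the document suggests such an imbalance, and the treatment is blinded.
- **The censoring is certainly informative.** The ban also covers other herbal products, and taking one need not signal coming progression.

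**Conclusion.** The concern holds as a minor conflict between the withdrawal rule and the imaging rule for the primary endpoint. It applies to prohibited therapy and to the other listed conditions that leave a patient reachable before progression; therapy given after progression is outside it.

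The cost is small. With 5 to 20 patients affected by prohibited therapy, which is an assumption because the document gives no rate, at most about 1.3 to 5.1 of 83 projected events are lost if withdrawal is unrelated to risk, or 0.5 to 2.3 points of power. Scaled to the stated 130 events, the loss is 2 to 8. It is larger if withdrawal signals coming progression: up to 2.7 to 10.9 events under a threefold hazard. The low power on 83 events comes from the sample-size section and adds no weight here.

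**What to change.** In Withdrawal/termination criteria, state that prohibited therapy, non-adherence, osimertinib toxicity and investigator decision end study treatment at most. State that only withdrawal of consent to follow-up, or unavoidable loss to follow-up, ends data collection. Add that patients who stop before progression continue the 8-weekly imaging of the PFS definition until progression or death. In Table 2, change the survival follow-up cell of the PFS row to: imaging per protocol until PD; record death.

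The cost is a wording amendment approved by the ethics committee, which can be made without looking at outcome data. Trial status reports 38 of 200 patients enrolled at July 2026, so most would be covered from entry. The other cost is scans for a few patients off treatment. Time from withdrawal to the month-24 cut totals 50.9 person-months for 5 patients and 206.8 for 20. At one scan per 1.84 months (8 weeks) that is at most about 28 or 112 scans, before allowing for progression. The PFS definition already plans them.

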### Interventions

#### Osimertinib intervention

According to the CSCO Guidelines for the Diagnosis and Treatment of Non-Small Cell Lung Cancer (2024) and the FLAURA trial (13), the recommended first-line osimertinib regimen for advanced EGFR-mutant NSCLC is 80 mg orally once daily, which can be taken with or without food (14). Treatment will be continued until disease progression, unacceptable toxicity, or other discontinuation criteria are met.

#### TCM intervention

The TCM intervention will be administered concurrently with EGFR-TKIs therapy and will continue until disease progression, unacceptable toxicity, or other criteria for treatment discontinuation are met. Both the YFXJD and placebo are manufactured as granules. Each sealed packet contains a fixed dose of granules (10 g per packet, 5:1 extraction ratio), with identical packaging to ensure complete blinding in terms of appearance, texture, smell, and taste. Matching placebo granules with similar appearance, odor, taste, and packaging, without active herbal ingredients. Are composed of pharmaceutical-grade excipients (primarily maltodextrin) with approved food colorants and flavorings.

Quality control of YFXJD granules includes: (1) botanical authentication of all raw herbs with voucher specimens deposited at the Shanghai University of TCM Herbarium; (2) compliance with Chinese Pharmacopoeia 2020 edition standards; (3) chemical fingerprinting by HPLC for batch-to-batch consistency; (4) 12-month stability testing; and (5) testing for pesticides, heavy metals, microbes, and adulterants. The YFXJD granules and placebo are produced under Good Manufacturing Practice (GMP) standards at Sichuan Neo-green Pharmaceutical Technology Development Co., Ltd. The manufacturer supplied the study products but had no role in study design, data collection, analysis, or manuscript preparation; no financial or non-financial competing interest exists.

Patients will be instructed to dissolve the contents of one packet in approximately 150–200 mL of hot water and to take it orally twice daily (morning and evening), 30 min after meals. The daily total dose will therefore consist of two packets. The dosage and administration frequency will remain constant throughout the treatment period unless modified due to tolerability issues as assessed by the investigator.

